### Measures

Phases 1 and 2 measures will involve using qualitative interview guides, informed by the extant literature and developed by the team, to identify important themes in the data. For phase 3, participants will complete the study assessment at enrollment (baseline) and at a 6-month follow-up, which will be digitally administered using iPads. The assessment will include self-report questions about HIV testing history, date(s) of previous testing, source(s) of previous testing, viral load, CD4 count, linkage and retention in care, TasP uptake, HIV medication, adherence and viral load if HIV-positive, and consideration of PrEP, including barriers and facilitators and its uptake, if HIV-negative. The assessment will also include measures that we will develop from the focus group data to assess participants’ knowledge, attitudes, and behavioral intentions toward TasP and PrEP use. Validated measures will include event-level characteristics of sexual risk episodes over the past 3 months, using the timeline follow-back interview method, with information on sexual activities, relationship with partner(s), partner gender, use of alcohol or drugs prior to or during, and use of condoms for each episode. Phase 3 will also involve fidelity monitoring of participants’ use of the intervention, including information about when they check or receive messages, whether they reply to messages or input information via messages, and whether they log calls to study staff.

### Study Outcomes

The primary outcome of the study will be levels of and increases in TasP or PrEP uptake in the intervention group compared with the control group, as determined by using assessment data from phase 3. Secondary outcomes include increases in levels of TasP- and PrEP-specific knowledge, favorable attitudes, and behavioral intentions regarding TasP and PrEP among participants in the intervention group. Lastly, we will explore decreases in sexual risk behaviors in the intervention group relative to the control.

### Planned Analyses

For the qualitative analyses in phases 1 and 2, we will independently read and code professional transcriptions of the focus groups and interviews, and will convene regularly to discuss emerging themes and systematically establish categories. Finalized thematic codes will provide an exhaustive categorization tool of concepts and themes described by participants. Multiple coders will analyze subsets of data, interrater reliability will be assessed, and any discrepancies will be resolved with discussion.

In phase 3, we will first assess the randomization process by comparing baseline demographic variables of participants in each arm; we will incorporate any variable for which randomization did not result in equal proportions in each arm into the multivariate models as a potential confounding variable. Next, we will conduct primary inferential analyses to test our primary hypothesis (ie, that messages sent over social media will increase TasP and PrEP uptake among the men in the intervention arm versus the control arm) followed by our secondary (increases in knowledge of, more favorable attitudes toward, and behavioral intentions regarding TasP and PrEP use between men in the intervention and control arms) and exploratory (decrease in sexual risk behaviors among men in the intervention arm in comparison with the control arm) hypotheses. Since the primary and tertiary outcome measures are binary, we will first compare proportions by randomization arm separately for each measurement period using standard bivariate analytic techniques (eg, Spearman rank-order correlations, odds ratios, and Fisher exact test). We will use ordinary least squares regression on our secondary measures of knowledge, attitudes, and behavioral intentions, which we will assess using continuous scales. We will contrast outcomes in the intervention versus comparison groups over time via generalized linear mixed models. Given the binary nature of our TasP and PrEP uptake and sexual risk measures, we will specify a logit link function for our generalized linear mixed models.

We will follow an intent-to-treat design and will include data from all enrolled participants in the analysis, regardless of level of intervention use. We will compare characteristics of participants who are lost to follow-up with those who are evaluated to assess for systematic patterns that could influence results. Following intent-to-treat principles, we will include all randomly assigned participants in the data analyses.

Effect-size estimates determined through the small RCT will be essential in the design of a larger and fully powered efficacy study that tests intervention effects on TasP and PrEP uptake and behavioral risk reduction. We are well aware of the limitations of relying exclusively on small-scale pilots to determine whether novel intervention approaches are promising, namely that sizable standard errors are associated with effect sizes due to the small sample size. However, we are primarily interested in exploring the pattern of results for any evidence of support for the intervention's influence on the primary and secondary outcomes. Our proposed sample size of 100 will be sufficient to detect an effect size of 0.3 or greater between the 2 groups, with 80% power and a 2-tailed alpha level of .05. Furthermore, we will be able to detect similar effect sizes (of ≥0.3) with respect to condomless anal intercourse and secondary analysis of social-cognitive behaviors.

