## Methods

### Study Design

This will be a 3-part study that includes focus groups and cognitive interviews to develop an eHealth intervention for HIV-positive and HIV-negative black and Hispanic MSM, and a small randomized controlled trial (RCT) to evaluate that intervention. In phase 1, we will use 4 to 6 focus groups of 5 to 8 participants each to learn about TasP, PrEP, and social media use in the target population, as well as obtaining feedback on an existing interactive website (Men2MenRI [33]). Members of our team previously developed the website targeting white MSM in Rhode Island. Phase 2 will use cognitive interviews with 8 participants and an open pilot with 16 participants to develop and assess the acceptability of IMB- and SCT-grounded social media message content designed to motivate and encourage access to our newly developed website. In phase 3, we will conduct a small RCT (n=100 participants, with 50 in each arm) comparing the combination of sending social media messages plus the website (active arm) versus the website alone (control arm). Study materials (eg, recruitment flyers, interview guides, questionnaires, website, and social media messages) and findings (eg, qualitative and quantitative data) will also be assessed by a community advisory board made up of 6 to 12 members from the local community who reflect the target groups. The study is approved by the Brown University Institutional Review Board (#1612001661), Providence, Rhode Island, USA, and the US National Center for HIV/AIDS, Viral Hepatitis, STD, and TB Prevention’s project determination process. This study is also registered on ClinicalTrials.gov (NCT03404531).

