We will randomly assign phase 3 participants to have access to either the website with social media messages (intervention condition) or the website alone (control condition). Participants will be stratified by race/ethnicity and HIV serostatus as in phases 1 and 2. We will use block random assignment in batches of 10, by HIV status and race/ethnicity, to keep the sizes of the intervention or comparison groups similar. Participants will physically come to the study site at enrollment for study description, consent procedures, website demonstration, randomization, demographic and HIV treatment and prevention history information collection, and baseline assessment; then they will come again 6 months later for the follow-up assessment. Participants will be assigned a research identification number, which will be used for all data collected to ensure confidentiality. Participants will be compensated in cash (all in US $) $40 for the focus group, $50 for the cognitive interview, $35 for the open pilot, and $80 for the small RCT ($40 for the baseline assessment and $40 for the 6-month follow-up) plus a potential $10 for transportation or child care costs incurred to attend study sessions. Eligible individuals will be allowed to participate in only 1 phase of the study.

Each phase of the study will provide unique information that will then inform the following phases. We will use focus group data from phase 1, which will include gathering feedback on the existing Men2MenRI website and to learn about TasP, PrEP, and social media use in the target populations, to create our new website and social media messages in a way that is audience specific. We will then use cognitive interviewing in phase 2 to further refine and develop the website and messages to be tailored to participant serostatus and race/ethnicity. Lastly, we will conduct an open pilot to evaluate and improve study procedures prior to the implementation of the small RCT in phase 3.

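### Baseline imbalance, not prognostic value or the randomisation strata, decides which covariates enter the adjusted models

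*Protocol article*

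**What the plan says.** All references are to the protocol article.

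- **Screening (Planned Analyses).** The phase 3 analysis begins with a check of the arms: "we will first assess the randomization process by comparing baseline demographic variables of participants in each arm". The number and names of these variables are not given.
- **Selection (Planned Analyses).** The team will then "incorporate any variable for which randomization did not result in equal proportions in each arm into the multivariate models as a potential confounding variable". No tolerance for equality is stated, and a variable need not be related to the outcome.
- **Models (Planned Analyses).** For uptake and sexual risk, "we will specify a logit link function for our generalized linear mixed models". For the continuous scales, "We will use ordinary least squares regression on our secondary measures of knowledge, attitudes, and behavioral intentions". Before the mixed models, the binary outcomes are compared between arms by simple bivariate methods.
- **Randomisation (Procedures and Interventions).** "We will use block random assignment in batches of 10, by HIV status and race/ethnicity". Nothing in the article commits these two factors to the models.
- **Size (Study Design).** "n=100 participants, with 50 in each arm".

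Observed imbalance is thus the only stated route by which a covariate enters a model.

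**The concern.** When allocation is random, a baseline difference between arms says nothing about whether the variable predicts outcome. A rule driven by imbalance has three weaknesses:

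1. It picks variables without regard to prognostic strength, so it forgoes most of the precision that adjustment can bring.
2. The covariate set cannot be written down until baseline data are seen by arm, and because *equal* is undefined there is discretion over what goes in.
3. It works against the design. The two stratification factors are kept close to balance by the blocks, so they are the variables least likely to qualify, although a model that follows stratified randomisation would normally contain them.

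What is at stake is the precision and prespecification of the adjusted estimates. In a logit model the covariate set also changes the conditional odds ratio being estimated. That matters because the article intends to carry the effect sizes into the design of a larger trial.

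**Working it through.** The article states no figure for this rule, so there is none to reproduce. The check asks what the rule does under each reading of *equal*, and then what it costs.

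**Inputs from the article:** 50 per arm; blocked randomisation stratified by HIV status and race/ethnicity; logit mixed models for binary outcomes and least squares for continuous ones.

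**Assumed, not in the article:** the number of screened variables (5 to 10, taken as independent), prevalences of 20% to 50%, and all simulation inputs in step 3.

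**1. Literal reading (identical proportions).** For a binary variable of prevalence p that was not stratified on, the chance of identical counts in two arms of 50 is the sum over x = 0 to 50 of [Binomial(x; 50, p)]².

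| p | P(identical counts) | P(enters the model) |
|---|---|---|
| 0.5 | 8.0% | 92.0% |
| 0.3 | 8.7% | 91.3% |
| 0.2 | 10.0% | 90.0% |

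So about 90% of such variables would enter. Whether that overfits the logit model depends on the number of uptake events, which the article does not project.

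**2. Significance-test reading (p < 0.05).** The chance that at least one of k independent variables is flagged is 1 − 0.95^k.

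- k = 5: 1 − 0.774 = 23%
- k = 8: 1 − 0.663 = 34%
- k = 10: 1 − 0.599 = 40%

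With k = 8 the expected number flagged is 8 × 0.05 = 0.4, and about 66% of trials flag none. Overfitting hardly arises on this reading.

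**3. Cost in precision for a continuous outcome.** The simulation had 50 per arm, eight independent standard-normal candidates, and one of them correlated ρ with the outcome. The true difference was 0.56 SD, which is what 50 per arm detects unadjusted with 80% power: (1.960 + 0.842) × √(2/50) = 0.56. There were 8,000 trials per scenario, and the rule was applied as p < 0.05.

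| ρ | Power, unadjusted | Power, imbalance rule | Power, prognostic covariate prespecified | Type I error, imbalance rule | Type I error, prespecified |
|---|---|---|---|---|---|
| 0.3 | 79% | 79% | 82% | 5.2% | 5.5% |
| 0.5 | 79% | 79% | 89% | 4.5% | 5.2% |
| 0.7 | 79% | 80% | 97% | 3.5% | 4.9% |

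The rule selected the one useful covariate in about 5% of trials at every ρ, which is the screening level itself.

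The gain from prespecifying agrees with theory. The standard error should fall from √(2/50) = 0.200 to 0.200 × √(1 − ρ²), that is 0.191, 0.173 and 0.143. The simulated standard deviations of the estimate were 0.190, 0.173 and 0.143. Under the rule they were 0.197, 0.196 and 0.188.

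**4. The strata.** Blocks within HIV status by race/ethnicity hold these factors near balance, apart from incomplete blocks. Under a significance test they would almost never qualify. Under the literal reading they would enter only if incomplete blocks happened to leave them unequal. Neither route is a commitment to include them.

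**The case against.** The strongest defence has five parts.

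- **The rule uses baseline data only.** It was published before phase 3 recruitment and never looks at outcomes. That stands, and it fits the finding of no type I error inflation.
- **An unadjusted comparison is planned first.** This also stands. A reader might infer that the primary result rests wholly on a model chosen after the fact. It does not, because the bivariate comparison of uptake is untouched by the rule.
- **The harms belong to different readings.** A reader might infer both that the model will be overloaded and that power will fall as in the table. The documents do not support the two together: overloading needs the literal reading, while the power figures use the 0.05 test. Identical proportions may not be what the authors meant, and a tolerance could sit in a fuller plan. But the rule itself is stated here, and any tolerance would still select on imbalance.
- **The power figures are for continuous outcomes under assumed correlations.** Agreed. They do not carry over to the binary primary outcome, and at ρ = 0.3 the gain is only three percentage points. The article does not show how strongly any covariate predicts outcome.
- **Some of the gain is already taken or not available.** Where baseline and follow-up are modelled together over time, the baseline value is already in use. For uptake, the phase 3 entry criteria leave little or no baseline variation. This limits the benefit mainly to the strata and to the least squares analyses.

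Pilot status lowers the stakes. It does not make the rule a sound one, since choosing covariates in advance is no harder in a small trial.

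**Conclusion.** The point holds in a limited form. The rule selects on chance, fixes the adjusted model only after baseline data are seen by arm, and tends to leave out the two factors on which randomisation was stratified.

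Its size depends on the reading. Literally, about 90% of unstratified binary demographics enter. As a 0.05 test, 23% to 40% of trials flag at least one of 5 to 10 independent variables, with next to no gain over no adjustment. For continuous secondary outcomes, the power forgone relative to a prespecified covariate is about 3, 10 and 17 percentage points at correlations of 0.3, 0.5 and 0.7, under the assumed inputs in the working.

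Two stronger conclusions are not supported. Type I error is not inflated: in the simulation it was 3.5% to 5.2%, so the test becomes conservative if anything. Overfitting of the primary model is a risk only if the literal reading applies and uptake events are few, and the article gives no event count from which to judge.

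Severity is modest: this is a small pilot whose authors already acknowledge large standard errors.

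**What to change.** Delete the imbalance rule and put a fixed covariate set in its place:

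- HIV serostatus and race/ethnicity, as the randomisation strata, in all models.
- The baseline value of the same outcome, where it varies and is not already modelled as a repeated measure. In practice this means the least squares analyses of knowledge, attitudes and intentions.
- The baseline table by arm presented descriptively.
- Any model that adds further imbalanced variables labelled as a sensitivity analysis.

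The cost is a sentence or so in the protocol or SAP. All these variables are already collected at enrolment, and neither the sample size nor the procedures change.

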## Introduction

### Background

There were an estimated 973,846 people living with HIV in the United States as of 2015; the US Centers for Disease Control and Prevention (CDC) further estimated that roughly 38,500 new infections occur annually [1]. Men who have sex with men (MSM) accounted for about 70% of those new infections in 2015, despite constituting just 2% of the country’s population [2]. Moreover, roughly 70% of the new diagnoses that year were in black and Hispanic MSM [2].

Black and Hispanic MSM continue to be disproportionately affected by HIV/AIDS in the United States. These racial and ethnic disparities in HIV/AIDS rates are also apparent in the Providence, Rhode Island Metropolitan Area, where new HIV/AIDS diagnoses among MSM increased between 2007 and 2011 even as total new diagnoses declined [3]. Moreover, 30% of individuals with a new diagnosis in Rhode Island from 2009 to 2013 also presented with AIDS, with MSM status being the leading risk factor, suggesting that a significant number of MSM in Rhode Island are only reaching care late in the course of their disease [3].

Effective biobehavioral interventions for HIV prevention in such high-risk populations include treatment as prevention (TasP) and preexposure prophylaxis (PrEP). TasP refers to the use of antiretroviral treatment to decrease the risk of HIV transmission between serodiscordant partners by reducing the viral load in the infected individual’s fluids to very low levels. TasP has been shown to have the potential to reduce HIV transmission to the partner without HIV by more than 96% [4]. PrEP is the daily ingestion of an oral single-tablet combination antiretroviral treatment by HIV-uninfected individuals. PrEP has been shown to have a greater than 90% chance of preventing HIV acquisition in adherent individuals, as confirmed by multiple studies [5-9]. However, knowledge about and uptake of PrEP and TasP remain low among black and Hispanic MSM [10,11]. Though results vary across studies, PrEP uptake is estimated at just 9.8% for black MSM and 6.6% for Hispanic MSM [12]. Barriers to PrEP uptake identified by previous research include lack of cultural competency in public health initiatives, stigma related to homosexuality and HIV serostatus, lack of targeted internet outreach, and low health literacy in the target populations [13].

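### If 6-month uptake is as low as the quoted PrEP rates, the uncapped covariate rule overloads the logit model for uptake and may overstate a real arm effect

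*Protocol article*

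**What the plan says.** The randomised phase is small: "n=100 participants, with 50 in each arm" (Study Design). The primary outcome is "levels of and increases in TasP or PrEP uptake in the intervention group compared with the control group" (Study Outcomes), so it pools HIV-positive and HIV-negative men.

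Under Planned Analyses, baseline demographics are compared between arms, and the authors will "incorporate any variable for which randomization did not result in equal proportions in each arm into the multivariate models". No threshold, maximum number or list of variables is given. Binary outcomes are first compared by arm at each assessment without adjustment, including a Fisher exact test and odds ratios. They are then modelled over time with generalised linear mixed models: "Given the binary nature of our TasP and PrEP uptake and sexual risk measures, we will specify a logit link function". The estimation method is not named.

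The only uptake figures are in Background: "PrEP uptake is estimated at just 9.8% for black MSM and 6.6% for Hispanic MSM". No TasP rate is given; the same section says only that "knowledge about and uptake of PrEP and TasP remain low among black and Hispanic MSM". Planned Analyses warns that "sizable standard errors are associated with effect sizes due to the small sample size", yet calls the pilot's effect sizes essential for designing the larger trial.

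**The concern.** A logit model needs enough events for the number of terms in it. With few events per parameter, ordinary maximum likelihood pushes a non-zero log odds ratio away from zero. A coefficient runs off to infinity when a category contains no events, or only events (separation). The rule sets no limit on the number of terms, and the quoted rates suggest that events may be few.

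The caveat in the article concerns imprecision. It does not cover an estimate pushed in one direction, or a model that fails and has to be rebuilt after the data are seen. If the adjusted odds ratio is carried into the next trial's design, an overstated effect makes that trial too small.

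**Working it through.** **The plan's own figure.** The article gives no event count to reproduce. Its one sample-size statement is an effect size of 0.3 with 80% power at N=100, on no named scale. As a standardised mean difference this gives 32% power; as a phi coefficient, 85%. Neither fixes the number of events, although phi=0.3 from the quoted control rates would imply 18-22.

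**Events at the quoted rates, applied to all 100 men (an assumption).** Expected events = 50 × control rate + 50 × active rate.
- No effect: 50 × 0.066 + 50 × 0.066 = 6.6; 50 × 0.098 + 50 × 0.098 = 9.8.
- Active rate doubled: 3.3 + 6.6 = 9.9; 4.9 + 9.8 = 14.7.

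This gives about 7 to 15 events.

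**Events if TasP uptake is higher.** Assume half the men are HIV-positive, PrEP uptake is 8.2% (midpoint of the quoted rates) and the odds ratio is 2. Control TasP uptake of 20%, 30% or 50% then gives about 19, 25 or 35 events.

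**How many variables enter.** For a binary variable with prevalence p and 50 men per arm, the chance of exactly equal proportions is the sum over k of [Binomial(k; 50, p)]². This is 11.2%, 8.7% and 8.0% for p = 0.15, 0.3 and 0.5. Read literally, about nine in ten binary variables enter.

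**Events per parameter (intercept not counted).**
- Arm + 9 terms: 7/10 = 0.7 to 15/10 = 1.5.
- Arm + 5 terms: 7/6 = 1.2 to 15/6 = 2.5.
- Arm + 2 stratification factors: 7/3 = 2.3 to 15/3 = 5.

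**Simulated arm odds ratio.** Settings: 100 men, 6-month data only, messages adding 10 percentage points, six non-prognostic demographics (nine terms) all entered. Fits in which the arm term diverged are excluded. The two values per cell are runs with different category splits (1,500 and 1,000 trials per case).

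| Control vs active | True OR | Maximum likelihood | Excess | Firth, same terms |
|---|---|---|---|---|
| 6.6% vs 16.6% | 2.82 | 3.61; 3.66 | 28%; 30% | 2.86; 2.88 |
| 9.8% vs 19.8% | 2.27 | 2.78; 2.70 | 22%; 19% | 2.29; 2.25 |
| 20% vs 30% | 1.71 | 1.88; 1.91 | 10%; 12% | 1.73; 1.74 |

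A third run gave 32%, 20% and 10%; a fourth gave 24-28% at the two low rates. In the first run, the root mean squared error of the log odds ratio fell from 0.97, 0.85 and 0.59 under maximum likelihood to 0.76, 0.66 and 0.50 under Firth.

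**Sensitivity to the number of terms (maximum likelihood; cases in table order).**
- Five binary demographics: excess 13%, 10% and 4% in one run; 8-9% in another.
- Only demographics with p<0.05 for imbalance: 10%, 6% and 3%.
- Arm plus the two stratification factors: 10%, 8% and 4%, with some coefficient diverging in 3.3%, 0.5% and 0% of trials. A second run gave 3-4% excess and 0.5-3.5% divergence at the low rates.
- Arm alone: 7%, 6% and 3%.

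**Divergence with the full set of covariates.** At 6.6-9.8%, some coefficient diverged in 5% to 69% of trials, depending on the rate, the effect and the covariate set; it was most frequent with no effect. The arm coefficient diverged in only about 0.3-8%. With a true odds ratio of 1, the arm estimate averaged about 1.0.

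**Empty cells.** The chance of no control events among 50 men is 0.934^50 = 3.3% or 0.902^50 = 0.6%. Among 25 men in one serostatus group it is 0.934^25 = 18% or 0.902^25 = 7.6%, and the sample odds ratio is then infinite or undefined.

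**The case against.** The strongest objection is that the event count borrows a rate from a different outcome. The quoted figures are for PrEP, whereas the outcome also counts TasP uptake, and neither a TasP rate nor the HIV-positive share is given. The eligibility wording for HIV-positive men is also ambiguous. This stands: a reader might infer that the data will hold only 7-15 events, and the article does not support that. At about 25 events or more, with arm, both stratification factors and three covariates, divergence was under 1% and the excess about 9% or less.

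Second, the size depends on a literal reading and on an assumed list of demographics. If the authors mean only notable imbalances, judged by a test, most of the excess disappears. This also stands, but nothing in the text limits the rule to that.

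Third, the Fisher comparison needs no model and is unaffected, and the article presents the trial as exploratory. Even a 28% excess (log 1.28, about 0.25) is small beside a root mean squared error of 0.97. True, but the Fisher test yields a p-value, not the adjusted effect estimate, and a bias in one direction is not covered by a warning about standard errors.

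Fourth, the estimation method and the handling of separation commonly belong in an analysis plan that is not shown. Their absence is therefore not the defect here. Maximum likelihood is inferred as the usual default, and the simulations use 6-month data, not the stated over-time model. The covariate rule, however, is fixed in the article itself.

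**Conclusion.** The point holds conditionally, as a cheap improvement. If 6-month uptake is near 6.6-9.8% in all men, the rule is read literally, about nine demographic terms enter and default maximum likelihood is used, a real arm odds ratio may be overstated by about 20-30%. At 20% uptake the figure is about 10-15%. It is less with fewer covariates, and there is no systematic excess when the messages have no effect.

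A reader might go further and conclude that the odds ratio is bound to be inflated, or that the arm effect will not be estimable. Neither follows. Divergence falls mostly on nuisance terms, and a diverging demographic coefficient does not by itself make the arm odds ratio meaningless. Nor is the unadjusted primary comparison undermined. Most of the excess comes from the number of covariates, so limiting them does most of the work; penalisation deals with what remains.

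**What to change.** In Planned Analyses, replace the imbalance rule for the uptake model with a fixed set of terms: arm plus the two stratification factors, serostatus and race/ethnicity. As a safeguard against sparse cells, fit the 6-month uptake model by Firth penalised logistic regression with penalised-likelihood intervals. Report the 6-month risk difference between arms with a score-type 95% interval (Newcombe or Miettinen-Nurminen), which stays defined when an arm has no events. Apply the same approach to any serostatus-specific estimate.

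The cost is a sentence or two of wording and standard software, with no added data or participants. The downside is slight shrinkage of the odds ratio toward 1 and fewer demographics adjusted for.

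### The article names ordinary least squares for the knowledge, attitude and intention scales without stating adjustment for the baseline score, which costs precision in a 100-man trial

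*Protocol article*

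**What the plan says.** Under Measures, "participants will complete the study assessment at enrollment (baseline) and at a 6-month follow-up", and the scales belong to that assessment: "The assessment will also include measures that we will develop from the focus group data to assess participants’ knowledge, attitudes, and behavioral intentions". A baseline score will therefore exist for each scale. Study Outcomes words the endpoint as a rise: "Secondary outcomes include increases in levels of TasP- and PrEP-specific knowledge, favorable attitudes, and behavioral intentions".

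Planned Analyses then states the method: "We will use ordinary least squares regression on our secondary measures of knowledge, attitudes, and behavioral intentions". No time point, change score or baseline covariate is given for that regression. The same section has one covariate rule: baseline demographics are compared between arms, and those that differ enter the multivariable models. It also plans to contrast outcomes between arms over time by generalized linear mixed models. A link function (logit) is given only for the binary outcomes, so it is unclear whether the scales enter those models.

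On size, Study Design says "we will conduct a small RCT (n=100 participants, with 50 in each arm". Planned Analyses says "Our proposed sample size of 100 will be sufficient to detect an effect size of 0.3 or greater between the 2 groups"; the power behind this claim is given as 80% and the two-sided alpha as 0.05. The claim is then extended to "similar effect sizes (of ≥0.3) with respect to condomless anal intercourse and secondary analysis of social-cognitive behaviors".

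**The concern.** For a scale measured before and after, the earlier score is usually the strongest available predictor of the later one. Using it as a covariate narrows the interval for the arm effect at no cost in data. The stated covariate rule does not bring it in, for two reasons. A scale score is not a demographic variable. The rule also acts only on observed imbalance, whereas the gain in precision depends on how well the covariate predicts the outcome, whether or not the arms look balanced.

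What is at stake is the width of the intervals for the secondary effects. The article accepts that standard errors will be large and says its main interest is the pattern of results on the primary and secondary outcomes. Part of that uncertainty can be removed with measurements already planned.

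**Working it through.** **Inputs.** 50 men per arm (Study Design); two-sided alpha 0.05 and 80% power (Planned Analyses); two assessments, baseline and 6 months (Measures). The correlation rho between the two scores is not in the article, so 0.3, 0.5 and 0.7 are assumed. The scale SD is set to 1 and taken as equal at both visits. No dropout is assumed.

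**The plan's own figure.** Read as a standardized mean difference, the natural metric for a continuous scale, an effect of 0.3 is not reproduced. The requirement is 2 × (1.960 + 0.842)² / 0.3² = 175 per arm, and 50 per arm gives about 32% power. The article does not name the metric. A correlation of 0.3, for example, would need about 85 men in all. That is a separate matter; it enters here only because baseline adjustment does not resolve it (last step).

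**Variance of the arm effect, relative to follow-up-only regression**
- Follow-up-only regression: 1
- Change score: 2(1 − rho)
- Baseline-adjusted (ANCOVA): 1 − rho²

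With two visits and complete data, the arm-by-time term of an unconstrained mixed model for a continuous scale equals the change-score comparison. The second line therefore stands for the over-time model, if that model covers the scales.

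**Detectable effect.** By the normal approximation, follow-up-only regression gives (1.960 + 0.842) × √(2/50) = 2.802 × 0.2 = 0.56 SD; with the t distribution it is 0.57 SD. The other values scale with the square root of the variance factor. The table uses the t distribution.

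| rho (assumed) | ANCOVA variance factor | SE against follow-up-only | Detectable effect, ANCOVA | Change-score variance factor | Detectable effect, change score |
|---|---|---|---|---|---|
| 0.3 | 0.91 | −4.6% | 0.54 | 1.40 | 0.67 |
| 0.5 | 0.75 | −13.4% | 0.49 | 1.00 | 0.57 |
| 0.7 | 0.51 | −28.6% | 0.40 | 0.60 | 0.44 |

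**ANCOVA against change score.** The ratio of standard errors is √[(1 − rho²) / (2(1 − rho))] = √[(1 + rho)/2]. At rho 0.5 it is √0.75 = 0.866, a cut of 13%. At rho 0.7 it is √0.85 = 0.922, a cut of 8%. It is below 1 for every rho below 1. At rho below 0.5 the change score is worse even than follow-up-only regression.

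**In power.** For a true effect of 0.5 SD, follow-up-only regression has 70% power. ANCOVA has 74%, about 82% and 93% at rho 0.3, 0.5 and 0.7. The change score has 55%, 70% and 89%.

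**Limit of the gain.** For 0.3 SD to be detectable with 80% power at 50 per arm, rho would have to be √[1 − (0.3/0.56)²], about 0.84.

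**The case against.** The strongest reply is that the omission is inferred. The article nowhere says that the baseline score is left out; it lists no terms for the regression, and a condensed article may leave the covariate list to the full protocol or analysis plan. The wording of the outcomes as increases, and the mixed model over time, both suggest some reference to baseline. A reader might infer that the scales will definitely be analysed with no use of baseline at all. The article does not support that.

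The reply does not remove the point. The article goes beyond silence: it states a model and a rule for choosing covariates, and that rule, read as written, does not admit the score. The references to increase and to change over time lead at most to a change score, which the working shows to be less precise.

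Two further readings are tempting and also fail. One is that the regression might pool both visits as if independent and so inflate the type I error; nothing in the article proposes this. The other is that imprecise scale effects would carry into the later, fully powered trial. The article ties that trial to uptake and behavioral risk reduction, not to these scales.

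It is also fair to say that the gain is small if rho is near 0.3, which cannot be excluded for scales not yet developed. And an ANCOVA restricted to men with follow-up would sit badly with the commitment to include everyone randomized. The fix below allows for that.

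**Conclusion.** The point holds as one of precision. The analysis as written does not state baseline adjustment for the scales, and neither the regression without the baseline score nor an unconstrained over-time contrast is as precise as a baseline-adjusted analysis. Against follow-up-only regression the avoidable excess in standard error is modest at rho 0.3 and substantial at rho 0.7. Against a change score the ordering reverses: the excess shrinks as rho rises. The sizes rest on the assumed rho, equal variances at the two visits, 50 men per arm and no dropout. Under randomization the estimates are not biased by leaving the baseline score out. Adjustment would not by itself make 0.3 detectable if that figure is a standardized mean difference.

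**What to change.** State one analysis for each scale, adjusted for the baseline score and for the stratification factors (HIV serostatus and race/ethnicity) regardless of observed imbalance. The better choice is a mixed model for both visits with a baseline mean common to the two arms, because it keeps every randomized man in the analysis, as Planned Analyses requires. The alternative is ANCOVA of the 6-month score with a stated approach to missing follow-up. Say that this replaces both the separate regression and any unconstrained over-time contrast for the scales.

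Procedures and Interventions lists randomization ahead of the baseline assessment at the enrollment visit. The plan should say that the scales are completed before allocation is revealed, so that the self-reported covariate cannot be influenced by knowledge of the arm.

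The cost is wording in the protocol or analysis plan and, if the listed order is the actual one, a change in the order of steps at enrollment. No new data are needed.
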